#### Missing Data

Our proposed primary analysis approaches are likelihood-based, which are valid under the missing-at-random mechanism; that is, the probability that an outcome is missing depends only on the observed variables included in the model. In such cases, no imputation of missing data will be necessary. However, we may conduct a sensitivity analysis to determine the sensitivity of our primary findings to key patterns of missing data, particularly patterns that are consistent with the missing-not-at-random mechanism, using pattern-mixture models [25]. Additional approaches such as multiple imputations will be used, as necessary. Similar results from the sensitivity analyses would strengthen our study findings, whereas different results would suggest that caution should be taken when interpreting our findings.

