### Power Analysis

Power analysis was based on the primary aim of this trial. Specifically, we calculated the sample size required to detect the effect of Joy Luck Academy on the primary outcome (quality of life at the 4-month follow-up assessment). In our primary analyses, we will use maximum likelihood-type (eg, restricted maximum likelihood) estimation procedures based on all observed data, assuming a missing-at-random mechanism [25]. The pilot study revealed that the Joy Luck Academy had an intermediate or higher effect on improving participants’ quality of life (Cohen *d*=0.47), depressive symptoms (Cohen *d*=0.55), and positive affect (Cohen *d*=0.62). On the basis of a targeted medium effect size of Cohen *d*=0.47, we estimated that a total sample size of 146 women at the 4-month follow-up would yield 80% power to detect this treatment effect at α=.05 (nQuery Advisor Version 7.0, Statistical Solutions Ltd). Assuming an attrition rate of 10%-20%, the final recruitment goal will range between 162 and 183 at the baseline.

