### Randomization

Participants who consent to participate will be randomly assigned to the Joy Luck Academy or control group at an approximate 1:1 ratio. Using minimization—a covariate adaptive randomization approach [26]—we will assign a participant to the intervention or control group by applying a randomization algorithm that will take into account participants’ age, stage of cancer, and time since completing treatment. This covariate information will be obtained by the HCA staff during the participant screening process. Randomization will start 4 weeks before the orientation scheduled start date and continue until the recruitment goal is reached or until 1 week before the start of each cohort study. Only the researcher conducting random assignments and the person who informs participants of their group allocation will be aware of the condition assignment.

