### Data Collection

#### Overview

After consenting, participants will complete the baseline questionnaires during an orientation session. These measures will be used to assess participants’ demographic and treatment information and psychosocial variables of interest. Participants’ demographic information (age, income, education level, and length of time living in the United States) and acculturation level [29] will be self-reported. Cancer and treatment information (cancer stage, treatments, and time since diagnosis) will be self-reported and confirmed through medical records, with participants’ consent.

Self-reported health outcomes and mediators will be measured via questionnaires at baseline, immediately after Joy Luck Academy completion and 1 month and 4 months after the intervention. The hypothesized moderating variables will only be measured at the baseline. The questionnaires, along with preaddressed, postage-paid envelopes, will be mailed to all participants. Participants will be asked to complete the questionnaires at home within 7 days and return them by mail. They will be reminded by phone to complete the questionnaires.

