### Data Analysis

#### Deductive Data Analysis Plan

Descriptive statistics and correlations among the major variables will be computed. The internal consistency of the questionnaires’ reliability at baseline will be assessed using Stata 16.0 software (StataCorp LLC). The construct validity of the questionnaires will be assessed using confirmatory factor analysis with Stata 16.0. Appropriate techniques (eg, exploratory factor analysis) will be used to improve reliability and validity, when necessary.

The primary analytic strategy will be multilevel analyses, also referred to as hierarchical linear modeling or linear mixed-effects modeling. Specifically, for each outcome variable, the primary independent variables of interest will include the intervention condition (experimental vs control), time (postintervention and 1- and 4-month follow-ups), and the interaction between the intervention condition and time. Random subject or Joy Luck Academy cohort effects, as applicable, will be used to model the correlations between repeated measurements within subjects and between observations from subjects within Joy Luck Academy cohorts. The selection of the random-effect covariance and serial correlation structure (eg, autoregressive correlation), as appropriate, will be based on the Bayesian information criterion. Each hierarchical linear modeling for assessing aim 1 will use quality of life as the primary outcome and other specified variables as secondary outcomes, controlling for the baseline outcome. In addition, results will be reported by controlling for important covariates used in the randomization (eg, age at baseline, cancer stage, and time since treatment) [50]. We will analyze the impact of the intervention on cortisol by testing the change in diurnal profile from pre- to postintervention using linear mixed-effects modeling. Cortisol outcomes will be indicated by raw cortisol values, initial levels, slopes, and areas under the curve, following previous methods [51-54].

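### With baseline FACT-G only as a covariate, the primary model drops women who have follow-up but no baseline, so it does not use all observed data

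*Protocol article*

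**What the plan says.** All places are in the protocol article.

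- **Power Analysis:** the primary analyses use "estimation procedures based on all observed data, assuming a missing-at-random mechanism".
- **Deductive Data Analysis Plan:** the model terms are arm, "time (postintervention and 1- and 4-month follow-ups), and the interaction between the intervention condition and time". Each model is fitted "controlling for the baseline outcome". Baseline is therefore a right-hand-side variable and not a level of the response.
- **Missing Data:** missing at random is defined for a missing outcome, given the observed variables in the model. Then: "In such cases, no imputation of missing data will be necessary". The section goes on to offer pattern-mixture sensitivity analyses, and multiple imputation where needed. It does not mention baseline values.
- **Randomization:** "Randomization will start 4 weeks before the orientation scheduled start date".
- **Data Collection, Overview:** after consent, "participants will complete the baseline questionnaires during an orientation session". The same section says that questionnaires are mailed to all participants, with telephone reminders.

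**The concern.** Likelihood methods accommodate missing responses. They do not accommodate a missing covariate unless that covariate is itself modelled. With baseline FACT-G on the right-hand side, a woman without it contributes nothing to a standard fit, even if all three of her follow-up scores are observed.

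The order of events makes this possible after randomization, because assignment can come up to four weeks before the orientation at which baseline is completed. A missing baseline would then remove a randomized woman from the primary analysis.

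Two things are at stake. One is some precision. The other is a possible departure from the randomized comparison, if the women without a baseline differ between arms in a way that is related to outcome.

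**Working it through.** **1. Reproduce the planned size.** Inputs from Power Analysis: d = 0.47, 80% power, α = .05; two-sided per the Deductive Data Analysis Plan; about 1:1 allocation per Randomization. The noncentral t calculation gives 72.04 per arm, rounded up to 73, total 146, power 80.5%. The stated 146 reproduces. With the 168 randomized given in the Abstract, 146 evaluable implies attrition of (168 − 146)/168 = 13.1%.

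**2. Confirm what the model does.** In a constructed data set of 146 women with 3 visits each (438 outcomes, all observed), 7 baselines were set to missing. The baseline-covariate mixed model, fitted to complete rows, used 139 women and 139 × 3 = 417 outcomes. It discarded 21 observed scores.

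**3. Size of the precision loss.** The article gives no rate of missing baselines, so 0% to 10% is assumed. Evaluable N = 168 × (1 − attrition) × (1 − share without baseline). Power is from the two-sample t test at d = 0.47, with no credit for baseline adjustment.

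| Attrition | 0% without baseline | 2% | 5% | 10% |
|---|---|---|---|---|
| 10% | 151; 81.9% | 148; 81.1% | 144; 79.9% | 136; 77.7% |
| 13.1% | 146; 80.5% | 143; 79.7% | 139; 78.5% | 131; 76.2% |
| 20% | 134; 77.2% | 132; 76.3% | 128; 75.0% | 121; 72.7% |

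At the planned 146, the cost is about 2 points at 5% and 4 points at 10%.

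**4. Credit the baseline adjustment.** With baseline-outcome correlation r (assumed; the article gives none), the effective effect is 0.47/√(1 − r²): 0.493 at r = 0.3, 0.543 at r = 0.5 and 0.588 at r = 0.6.

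| r | Power, no loss (146) | Power, 10% lost (131) |
|---|---|---|
| 0.3 | 84.1% | 80.0% |
| 0.5 | 90.3% | 87.0% |
| 0.6 | 94.1% | 91.7% |

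The loss is still about 2 to 4 points, but power stays at or above 80% for r of about 0.3 or more.

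**5. Bias.** This was a single-outcome ANCOVA simulation with assumed r = 0.6, true effect 0.47 and N = 146. With 2% to 10% of baselines missing completely at random, the complete-case estimate was 0.469 to 0.471, so there was no bias. Under a constructed mechanism in which about 10% of controls (mainly those with low outcomes) and 2% of intervention women lacked a baseline, the complete-case estimate was 0.426, which is 0.044 too low. Filling with the pooled baseline mean gave 0.496, which is 0.026 too high. In that scenario missingness depends only on arm and the observed outcome, so a joint likelihood with baseline as a response would treat it as missing at random.

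**The case against.** - **The no-imputation sentence is conditional.** It refers back to missing outcomes under missing at random, and there it is correct for a likelihood analysis. This stands. A reader might infer that the sentence is false, but the text does not support that. The gap is that its condition says nothing about a missing baseline, while its wording covers missing data in general.
- **Multiple imputation is allowed where needed.** This stands so far as the plan does not rule out imputing a baseline, and nowhere does it say that such women are to be deleted. But that allowance sits among the sensitivity analyses and does not name baseline or the primary model.
- **Missing the orientation need not mean a missing baseline.** Questionnaires are also mailed, with reminders, so the rate could be close to zero. This stands, and it limits the size of the point.
- **A reader might infer that controls, once told of the self-study group, skip baseline more often and bias the contrast.** The article does not say when women learn their allocation, and gives no sign of different attendance by arm. The 0.426 estimate comes from an assumed mechanism and is not evidence about this trial.
- **A reader might infer that the trial becomes underpowered.** At the planned 146, power falls below 80% only if the planned baseline adjustment is ignored or r is small. Some women without a baseline may also already fall within the 10% to 20% attrition allowance.
- **Handling of a missing covariate is usually left to the statistical analysis plan.** This is fair as to the detail. What remains is that the article fixes a model that does not deliver the all-observed-data property it claims.

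**Conclusion.** The point holds as a minor mismatch between the fixed model and its description. With baseline as a covariate only, a standard fit excludes randomized women who have follow-up but no baseline, and the order of randomization and orientation allows such women to exist.

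At an assumed 5% to 10% missing, the cost is about 2 to 4 power points, and power may remain at or above 80% once adjustment is credited. Bias in the arm contrast would need missingness that differs by arm and is related to outcome, and the documents do not show this. The conclusion rests on two assumptions: that some baselines are missing, and that the model is fitted in the usual way, with incomplete rows dropped. If no baseline is missing, nothing changes.

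**What to change.** 1. Count the randomized women who have at least one follow-up FACT-G score but no baseline. Data collection is complete, so this needs no new data.
2. State that the primary analysis keeps every randomized woman with any follow-up score, in one of two ways:
   - put baseline in the response vector, with arm means constrained equal at baseline. This is preferable because it extends the likelihood argument that the plan already uses; or
   - keep baseline as a covariate and fill missing values with the pooled baseline mean, ignoring arm.
3. Limit the no-imputation sentence to missing follow-up outcomes. The all-observed-data wording then becomes accurate.
4. State whether women were told their group before completing baseline, since both options assume that baseline scores were not affected by knowing the allocation.

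The cost is a few lines of model code and text. Results are essentially unchanged if no baseline is missing.

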#### Qualitative Data Analysis

The interviews will be transcribed and analyzed in Chinese to preserve the linguistic meanings and enhance the trustworthiness of the data. In the thematic analyses, we will code responses, extract broad themes, and identify subthemes [58].

## Results

Recruitment began in February 2015, and all data collection was completed by February 2019. We expect to complete data management by August 2021 and submit the study results for publication by 2022.

## Discussion

Few evidence-based psychosocial interventions designed for diverse ethnic groups of cancer survivors are available. This study is the first RCT to test a culturally sensitive social support intervention in Asian American (specifically, Chinese immigrant) breast cancer survivors. In this trial, we will determine the health benefits of a 7-week education and peer mentorship intervention on quality of life, depressive symptoms, positive affect, and other outcomes in Chinese American breast cancer survivors immediately after the intervention and at 1- and 4-month follow-up assessments. These individuals may benefit from interventions tailored to their needs for survivorship health care information [10] and social support [7]. This program has the potential to be adapted for other Asian American immigrant breast cancer survivors and eliminate unnecessary emotional and physical health disparities in cancer care.

The design of this study has both strengths and limitations. The intervention is innovative, as it is culturally relevant to an ethnic group and uses a theoretically grounded CBPR approach. As this study targets breast cancer survivors who have completed treatment, cancer patients undergoing active treatment will not be enrolled in the study, which limits its generalizability. The Joy Luck Academy is specifically designed to meet the needs of Chinese American breast cancer survivors and, therefore, may not be directly applicable to survivors of other ethnic groups. Future studies are needed to test this type of intervention in other minority groups.

If the Joy Luck Academy is demonstrated to improve the well-being of Chinese American breast cancer survivors, it may be disseminated to this population across the country.

## Abbreviations

CBPR: community-based participatory research
CES-D: Center for Epidemiologic Studies Depression
FACT-B: Functional Assessment of Cancer Therapy-Breast
FACT-G: Functional Assessment of Cancer Therapy-General
HCA: Herald Cancer Association
RCT: randomized controlled trial
